| Abstract | Chronic pelvic pain syndrome (CPPS) has a high incidence and can present with severe symptoms, leading to mental health issues, causing anxiety, depression, and pain catastrophizing, and placing significant stress on families and society. The exact causes and mechanisms of CPPS remain unclear; studies suggest it may be caused by psychological issues and multi-system dysfunction. Therefore, addressing psychological problems is crucial in the treatment of CPPS. Repetitive peripheral magnetic stimulation (rPMS) shows potential effectiveness in treating CPPS, while repetitive transcranial magnetic stimulation (rTMS) has been proven to be effective for anxiety and depression. This study employs a randomized, double-blind method, recruiting 66 CPPS participants with accompanying psychological issues, who are stratified by gender and randomly assigned to three groups (1:1:1): double-target magnetic stimulation group, peripheral magnetic stimulation group, and sham stimulation group, receiving the corresponding treatments. The efficacy and safety of double-target magnetic stimulation in CPPS patients with psychological disorders will be assessed by comparing changes in pelvic pain scores (for females) or the National Institutes of Health Chronic Prostatitis Symptom Index (NIH-CPSI, for males), depression, anxiety, and stress scales (DASS-21), pelvic floor surface electromyography, pudendal nerve motor evoked potentials, and the 36-item Short Form Health Survey (SF-36) scores before and after treatment. | | | | | | | | | | |
| Keywords | | Repetitive Transcranial Magnetic Stimulation, Repetitive Peripheral Magnetic Stimulation, Chronic Pelvic Pain Syndrome, Randomized Controlled Trial | | | | | | | | | |

**三.**Project Team Members (including Principal Investigators)

| Name | Unit | Dgree | Title | Task division | Ethics training | GCP training | Signature |
| --- | --- | --- | --- | --- | --- | --- | --- |
| [name] | Chengdu Anorectal Hospital | Master's degree | Associate Chief Physician | Project Leader | Yes | Yes |  |
| [name] | Chengdu Anorectal Hospital | Doctor | Professor | Project Guidance | Yes | Yes |  |
| [name] | Chengdu University of Traditional Chinese Medicine Affiliated Hospital | Doctor | Chief Physician | Supervision of Project Implementation | Yes | Yes |  |
| [name] | Sichuan Province Fifth People's Hospital | Master's degree | Attending physician | Data organization, statistical analysis | Yes | Yes |  |

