5.1 Sample Size Estimation

According to the research by Yang Jing-ming and his colleagues, under the conditions of β=0.1 and α=0.05, the effect size is 0.5. Pain scores will be used as the primary measurement standard, and G*Power 3.1.9.7 will be used to estimate the sample size. It is calculated that there will be approximately 54 patients in the study cohort, and considering a 10% dropout rate, each group will include 22 people, requiring a total of 66 participants for this RCT.

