11.1.2 Case Report Form (CRF)

In clinical trials, it is necessary to record the specified observations or examination items in the case report form. The case report form includes...

The content must be completely consistent with the original data, and the basis for the results calculated from the original data should be traceable.

When filling out, you must meet the following standards:

(1) Fill in with a black signature pen or black ballpoint pen;

(2) Cases that have already signed the informed consent form and meet the inclusion criteria should fill out the case report form, even if they have not received treatment or are determined to not meet the inclusion criteria after treatment.

(3) When making corrections, the original record must be crossed out with a line (correction fluid or similar cannot be used), but the original record must remain legible. Additionally, the person making the correction must sign at the correction point and indicate the date of the correction.

(4) For unexamined items, it must be marked as "ND (Not Done)".

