11.2 Statistical Analysis

11.2.1 Analysis of Population Definition:

The patients who were enrolled and received treatment constitute the intention-to-treat population (ITT) for this trial. The population and the patients who comply with the requirements of this clinical trial protocol and complete this study constitute the per protocol population (PP). The statistical analysis will use intention-to-treat (ITT) for missing data, comparing the "full analysis set (FAS)" and the "per protocol set (PP)."

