11.2.2 Statistical Analysis Methods

Statistical analysis will be conducted using SPSS 27.0 software. Continuous data will be presented as mean ± standard deviation. Paired t-tests will be used for inter-group comparisons, and repeated measures ANOVA will be used for intra-group comparisons, including before and after treatment and during follow-up. Statistical significance will be indicated by a P value < 0.05. If there is a reduction in personnel during the trial, an intention-to-treat (ITT) analysis will be performed, comparing the "full analysis set (FAS)" and the "per-protocol set (PP)."

12. Data Confidentiality Plan

Participation in the trial and personal information during the trial are confidential. Information that can identify the subjects will not be disclosed to anyone outside the research team unless permission is obtained from the subjects. All research members and sponsors are required to keep the identities of the subjects confidential. The subjects' files will be stored in a locked filing cabinet and will only be accessible to researchers. To ensure that the research is conducted according to regulations, government regulatory agencies or members of the ethics review committee may review the subjects' personal information at the research site as necessary. When the results of this study are published, no personal information about the subjects will be disclosed.

13. Ethical Requirements and Informed Consent

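### ITT is named as the way missing data are handled, but the repeated measures ANOVA drops any patient who lacks one modelled visit, so the longitudinal result covers complete attenders only

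*Protocol*

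**What the plan says.** Section 11.2.1 defines the ITT population as patients who were enrolled and treated, with no condition on visits attended. The same section says that "The statistical analysis will use intention-to-treat (ITT) for missing data". Section 11.2.2 repeats ITT as the response to attrition, with a comparison of the full analysis set (FAS) and the per-protocol (PP) set.

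For the longitudinal analysis, section 11.2.2 specifies SPSS 27.0 and says that "repeated measures ANOVA will be used for intra-group comparisons, including before and after treatment and during follow-up".

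Section 7 and Appendix 2 place all five efficacy measures at six time points, t0 to t5. Section 5.1 gives "approximately 54 patients in the study cohort, and considering a 10% dropout rate, each group will include 22 people", 66 in total.

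Two other places touch on missing data. The SF-36 form in Appendix 6 substitutes an average for a missing item within a domain, and Appendix 2 has a row at t5 for analysing missing items and non-respondents. Neither supplies a value for a missed visit. No imputation rule, last-value rule or likelihood method is stated.

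**The concern.** The protocol offers a population where a method for missing values is needed, and then names a model that cannot use an incomplete row. Followed as written, the analysis labelled ITT discards every observed score of a patient who missed one modelled visit.

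Two things are at stake. Observed data are lost in a trial of 66 patients. The patients who remain are also selected on attendance, which may depend on pain, mood or response. The selection can differ between outcomes, because the questionnaires, the rectal-electrode electromyography and the evoked-potential test need not be missed together. In addition, the FAS and PP longitudinal results would both rest on patients with complete visits, which weakens the comparison that the protocol plans between them.

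**Working it through.** **Inputs.** 66 randomised, 22 per arm, 54 required (section 5.1). Six time points (section 7, Appendix 2). The per-visit miss rate *m* is not in the protocol; 5% and 10% are assumed, independent across visits, with baseline complete. The number *k* of post-baseline time points in the model is not spelled out: *k* = 5 if t0 to t5 all enter, *k* = 2 if only t0, t4 and t5 do.

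**Step 1: the plan's own figure.** Section 5.1 states "under the conditions of β=0.1 and α=0.05, the effect size is 0.5". Reading 0.5 as Cohen's f in a one-way ANOVA of three arms, the noncentrality is N × f² = 54 × 0.25 = 13.5. On 2 and 51 degrees of freedom this gives power 0.902; N = 51 gives 0.882. The 54 is reproduced, as the size for a between-arm test.

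**Step 2: what the method does with a missing cell.** A classical repeated measures ANOVA needs a value at every modelled level for each patient. As a check, a standard routine was given 22 subjects at six visits with one cell removed; it refused to fit because the data were unbalanced. This is a property of the method, not a statement in the protocol.

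**Step 3: patients with complete rows.** Formula: 66 × (1 − m)^k.

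| m (assumed) | t0 to t5, k = 5 | t0, t4, t5 only, k = 2 |
| --- | --- | --- |
| 5% | 66 × 0.7738 = 51.1 | 66 × 0.9025 = 59.6 |
| 10% | 66 × 0.5905 = 39.0 | 66 × 0.81 = 53.5 |

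**Step 4: break-even with the stated 54.** Formula: m = 1 − (54/66)^(1/k). This gives 3.9% for k = 5 and 9.5% for k = 2.

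**Step 5: if the planned 10% dropout also occurs.** 66 × 0.9 = 59.4 patients are left before any occasional miss. The break-even 1 − (54/59.4)^(1/k) is then 1.9% for k = 5 and 4.7% for k = 2.

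**Step 6: per arm.** Section 11.2.2 applies this ANOVA within groups, so the arm is the relevant unit. Of 22 patients, 22 × 0.7738 = 17.0 or 22 × 0.5905 = 13.0 remain for k = 5 at 5% and 10%; for k = 2, 22 × 0.9025 = 19.9 or 22 × 0.81 = 17.8.

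**The case against.** The strongest reply is that an ITT population and repeated measures ANOVA are compatible once missed visits are imputed, and that the imputation method is commonly left to a statistical analysis plan, which may exist. This is fair as far as it goes: the protocol is not at fault for omitting detail. But it does not stay silent. It names ITT as the handling of missing data and fixes the model, and those two statements together lead to complete-attender results.

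A second reply concerns size, and much of it stands. The t1 to t4 assessments fall at the end of treatment weeks, when patients already attend five days a week, so occasional misses may be rare. Section 3.3 withdraws patients who do not adhere to treatment. Misses that cluster within the same patients would cost fewer complete rows than the independence formula gives. The instruction in section 11.1.2 to mark unexamined items as not done is general form-filling guidance, not evidence that missed visits are expected.

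Three stronger readings are tempting and are not supported:
- **All six visits certainly enter one model.** Section 11.2.2 does not say so. Its wording also fits t0, t4 and t5 only, and on that reading a missed t1, t2 or t3 removes nobody.
- **The trial's power falls below 90%.** The stated 90% matches a between-arm F test, whereas section 11.2.2 assigns this ANOVA to within-group comparisons and gives between-group comparisons to t-tests. Fewer complete rows in the former cannot be read off the power curve of the latter.
- **The FAS-versus-PP comparison becomes empty.** PP also requires compliance with the protocol, and the t-test comparisons can still differ between the two sets.

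**Conclusion.** The point holds. ITT is not a missing-data method, and as written the longitudinal analysis would be restricted to patients with every modelled visit, whatever the population is called. For that analysis the FAS loses much, though not all, of its distinction from the PP set.

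The size is conditional. With independent misses of 5% to 10% per visit, about 51 to 39 of 66 patients remain if t0 to t5 are all modelled, and about 60 to 53 if only t0, t4 and t5 are. At low miss rates, or with misses concentrated in a few patients, the loss is small. The direction of any bias cannot be determined from the protocol. The change is worth making because the remedy is cheap and keeps data that will already have been collected.

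**What to change.** In section 11.2.2, replace repeated measures ANOVA with a linear mixed model, available in SPSS, that uses all observed visits and includes arm, visit, arm-by-visit and baseline score. The primary outcome needs care. Women are scored on sixteen 0–10 items (Appendix 3) and men on the NIH-CPSI, with a total up to 43 (Appendix 4), so one model of the raw score with a sex term would average unlike units. Fit the model separately by sex and instrument, or on a prespecified standardised scale. For outcomes measured on the same scale in both sexes, include sex as a covariate. State which time points enter the model.

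In section 11.2.1, replace the clause on ITT for missing data with a statement that all patients in the ITT set with observed data are analysed, that missed visits are handled by likelihood under missing-at-random, and that a sensitivity analysis assumes worse outcomes for missing t4 and t5 values.

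The cost is a few sentences and slightly more analysis work, with the same software and no new data. The main result then relies on the missing-at-random assumption, which cannot be verified and is the reason for the sensitivity analysis.

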13.1 Obtain approval from the ethics committee

Before initiating clinical trials at a research institution, approval from the institution's ethics committee must be obtained. During the trial, researchers are required to submit progress reports to the ethics committee, and after the trial concludes, a written report should also be provided to the ethics committee.

13.2 Informed Consent

Before the case registration, the principal investigator or researchers explain the relevant content of the clinical trial to the subjects according to the informed consent form, and then provide the subjects with sufficient time to consider it. The subjects then independently decide whether to sign the informed consent form. The principal investigator or researchers and the subjects sign the informed consent form and indicate the date (specifying the date of obtaining informed consent). If trial-related personnel provide additional explanations, they must also sign or write their name and stamp it, and record the date of the explanation. Furthermore, if there are changes to the trial protocol during the trial, or if new information arises that may affect the subjects' decision to continue participating in the trial, the subjects must be informed of the changes, and they must again independently decide whether to sign a new informed consent form. If the subjects do not agree to sign the new informed consent form, they must withdraw from the clinical trial. The informed consent form is made in duplicate, with the original kept by the center and a copy retained by the subjects.

13.3 Revision of the Informed Consent Form

The principal investigator may consider modifying the informed consent form based on the latest information. The revised informed consent form must be approved by the ethics committee before it can be used in the clinical trial. Patients who have signed the old informed consent form and have not completed the clinical trial should sign the new informed consent form again before continuing with the trial. Both the new and old versions of the informed consent form must be retained as original documents.

13.4 Protection of Participants' Privacy

In case report forms, statistical analysis reports, clinical trial reports, and adverse event reports, any content that involves patient information must not include the patient's real information. Patients can be identified through numbers and initials.

13.5 Modification of the Research Plan

This plan, after being approved by the ethics committee, requires that if there are significant modifications during the implementation process, the clinical research leader must write a "Protocol Amendment Document" and sign it. Additionally, it must be submitted for approval by the ethics committee before implementation. If there are no fundamental changes, the clinical research team, statisticians, and methodologists will discuss and decide together and sign.

14. Quality Control and Quality Assurance

14.1 Data Management

All selected cases must have the CRF (Case Report Form) completed by a designated physician, and all items in the CRF must be filled out. The filled items must not be altered; if a correction is needed, the incorrect data should be crossed out with a short horizontal line, and the correct result should be written above it, along with a signature and the date of the correction. After completing the form, the physician should carefully check and verify all data in the CRF and sign the form to indicate that it has been reviewed, ensuring the authenticity and accuracy of the data filled in. The completed CRF will be reviewed by the monitor and then kept for data entry and management.

14.2 Quality Control of This Study

Control content: Check if there are any omissions in the filling of indicators, whether it is consistent with the original data, and whether it is filled out accurately.

Frequently Asked Questions: Low consistency in completion by different doctors; missing or incorrect entries, and inconsistencies with research cases.

Solution: Before the start of this study, the participating doctors and staff must undergo standardized training, with uniform recording methods and judgment criteria. Ensure the consistency, reliability, completeness, and accuracy of the evaluation indicators. During the study, monitors appointed by the Principal Investigator (PI) will conduct regular monitoring visits and audits to ensure strict adherence to all aspects of the study protocol, the correctness of the Case Report Form (CRF) completion, and the authenticity and accuracy of the data recorded.

14.3 Preservation of Original Data

The original data of this study, including signed informed consent forms, relevant clinical scales, laboratory test reports, functional examination reports, case records, and other related records, should be kept in the archives of Chengdu Anorectal Specialty Hospital.

14.4 Setting up the experimental blind method

A researcher will place the random sequence numbers generated by SPSS software into opaque envelopes separately and number the envelopes in order on the surface. This researcher will not participate in other studies and will ensure that the envelopes containing the random sequence numbers remain sealed throughout the research process, so that other personnel will not know the random sequence numbers inside the sealed envelopes in advance. A second researcher will select eligible patients for the study based on inclusion and exclusion criteria. Patients will be informed of the potential benefits and risks of the study, and if they agree to participate, they will sign an informed consent form. The third researcher will ask patients about their condition, assess their status, assist in filling out the CRF forms, and distribute the envelopes to the patients participating in the study. The fourth researcher will treat patients according to the random sequence numbers in the envelopes given to them and will not participate in other studies. The fifth researcher will evaluate and complete the pelvic pain scale (for women) / National Institutes of Health Chronic Prostatitis Symptom Index (NIH-CPSI) (for men), the DASS-21 scale, and the SF-36 quality of life scale assessments, and will complete the patients' pelvic floor surface electromyography and pudendal nerve motor evoked potential tests. This researcher will not participate in data analysis or other studies. After data collection is completed, the first unblinding will occur, with two researchers entering and verifying the data separately. Finally, a statistical analyst will conduct the statistical analysis, comparing the three groups without knowing the group assignments. After the analysis is completed, a second unblinding will take place, marking the end of the study.

15. Preservation of Data and Records

Researchers are responsible for ensuring that research records are not accidentally damaged; the medical records of subjects should be clearly labeled to prevent accidental destruction of documents due to errors. Researchers and research institutions must retain clinical trial-related materials for five years after the conclusion of the clinical trial. Original medical documents should be kept according to the relevant regulations of the hospital, but must not be less than five years after the conclusion of the clinical trial.

16. Research Process

All subjects must meet the diagnostic criteria for CPPS according to EAU and the diagnostic criteria for generalized anxiety disorder or major depressive disorder according to DSM-5. Subjects who are determined to meet the inclusion criteria and do not fall under the exclusion criteria are considered potential subjects. The screening physician will inform the subjects and their families about the study, explain the differences in treatment, and seek the opinions of the subjects and their families on whether they agree to random grouping. Patients who agree to random grouping will sign an informed consent form and will then be included in the study for random grouping and will receive follow-up after the treatment course. (See Appendix 1)

17. Summary report and paper publication

(1) After completing the research summary of the clinical study, papers can be published and participation in domestic and international academic conferences is possible.

(2) The results of this research will be published in the form of papers. It is expected to publish 1-2 SCI papers.

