11.1 Data Processing

11.1.1 Data Collection

All data should be recorded in a timely, truthful, and detailed manner in the Case Report Form (CRF). Researchers must input information into the CRF according to the protocol requirements. The research center will assign a supervisor to check the completeness and accuracy of the CRF and guide the research center staff in making necessary modifications or additions. The CRF will be submitted to data processing by the research supervisor, with one copy retained at the research center and another attached as the supervisor's work document. The CRF will be handed over to two reliable medical data processors for data entry and verification. The case report form should be filled out by a designated person from the unit and signed by the project leader of the unit to be considered a valid case. After the clinical trial is completed, a clinical summary report should be written according to the requirements of the clinical summary guidelines.

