11.1.3 Database Management and Quality Control

The data items in the CRF will be entered into the research database using a double-entry verification method. Text items (such as comments) can only be manually verified after being entered once from the CRF. Subsequently, data managers conduct systematic checks on the information in the input database using error messages printed from the confirmation procedures and database lists. If necessary, a separate document provides clear instructions for special operations related to the handling and archiving of the DQF (Data Quality Form) for the trial (such as confirmation plans). The database will be locked once it is declared complete and error-free. After that, any changes to the database can only be made with the joint written consent of the clinical research leader, research statistician, and data manager. The interpretation of results will be conducted by a third party who is unaware of the patient grouping, ensuring the objectivity of the results.

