Randomization results for eligible participants:

Group A (dual-target magnetic stimulation) □

Group B (peripheral magnetic stimulation) □

Group C (sham stimulation) □

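### Section 14.4 puts the first unblinding before data entry and database lock without saying what it reveals, so the analyst's blinding is not secured if the letters printed in Appendix 7 are used

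*Protocol*

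**What the plan says.** Section 14.4 of the protocol sets out a two-step unblinding. The first step is tied to the end of data collection: "After data collection is completed, the first unblinding will occur, with two researchers entering and verifying the data separately". The analysis follows: "Finally, a statistical analyst will conduct the statistical analysis, comparing the three groups without knowing the group assignments". The last step is then: "After the analysis is completed, a second unblinding will take place, marking the end of the study".

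The data-handling sections describe the same period from another side. Section 11.1.1 says: "The CRF will be handed over to two reliable medical data processors for data entry and verification". Section 11.1.3 describes double entry, systematic checks by data managers and then the lock: "The database will be locked once it is declared complete and error-free". It adds a further safeguard: "The interpretation of results will be conducted by a third party who is unaware of the patient grouping".

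Appendix 7, the randomisation application form, has a field for the random number and three tick boxes for the result. Each box gives a letter with the arm beside it: "Group A (dual-target magnetic stimulation") for the first, "Group B (peripheral magnetic stimulation") for the second, and sham stimulation as Group C for the third.

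**The concern.** In a two-step scheme the first step normally releases group codes so that the groups can be compared, and the second releases what the codes mean. That protects the result only if the data are final before the first step and the codes mean nothing to those who receive them. The protocol secures neither condition.

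Decisions that call for judgement remain open when data collection ends. The CRFs are completed by hand (section 11.1.2), so entry and verification involve reading and querying written entries. The per-protocol set in section 11.2.1 consists of those who complied with the protocol and completed the study, and sections 11.2.1 and 11.2.2 rely on a comparison of the full analysis set with that set. If group information is available while such points are settled, the handling of queries or of per-protocol membership could differ by group, and nothing in the final data set would show it.

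**Working it through.** No arithmetic applies. The check sets the sections side by side.

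**Step 1: the order of events.** Section 14.4 gives: data collection complete; first unblinding, with entry and verification alongside or after it; analysis; second unblinding. Section 11.1.3 gives: double entry; systematic checks; lock. Both contain entry and verification, so they can be joined there:

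1. data collection complete (14.4)
2. first unblinding (14.4)
3. double entry and verification, alongside or after step 2 (14.4, 11.1.3)
4. systematic checks (11.1.3)
5. database lock (11.1.3)
6. analysis (14.4)
7. second unblinding (14.4)

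The joined order puts the first unblinding ahead of lock. Neither section makes lock a condition for it. This result rests on the stated order alone.

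**Step 2: what the first unblinding releases.** Section 14.4 names neither the content nor the recipients. There are three possibilities.

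- *It releases the arms by name.* Anyone who receives them during data entry works with the arms known. The analyst stays blind only if the information is kept from the analyst, and no such arrangement is described.
- *It releases the letters A, B and C.* These are the only group codes in the protocol. Appendix 7 prints the arm beside each letter, so even the blank form is a key. Recipients can identify the arms, and the second unblinding has nothing left to reveal.
- *It releases neutral codes that the protocol does not mention.* The analyst can then be blind as stated. Group membership would still be available, in coded form, before the data are final.

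**Step 3: what follows.** Under all three readings an unblinding step precedes lock. Under the first two, the blinding of the analyst in 14.4 and of the interpreter in 11.1.3 is not secured. Only the third keeps the stated blinding, and the document describes no such codes and no holder of a key.

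**The case against.** A reader might infer that the analyst's blinding fails outright and that all 66 records are exposed. The documents do not support that. Section 14.4 states that the analyst works without knowledge of the assignments and places a second unblinding after the analysis, which points to an intended scheme of codes first and meaning second. That the first step releases the Appendix 7 letters is an inference. No section sends the completed Appendix 7 form to the data processors or the analyst; what section 11.1.1 hands over is the CRF. A trial must record allocation somewhere, and a record that names the arm does not in itself break the analyst's blinding.

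A reader might also infer that the subjective primary scales are at risk. They are not at risk from this step. Data collection is complete by then, and the scales are scored by a separate researcher who takes no part in data analysis. Nor does any section have an unblinded person choosing the models: section 11.2.2 names methods in advance.

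Other safeguards count as well. Corrections to the CRF must be signed, dated and leave the earlier entry legible. The physician checks the form, and the monitor reviews it, before entry (section 14.1). Entry is double. Changes after lock need the joint written consent of three roles. When and by whom the per-protocol set is classified may properly be left to a statistical analysis plan that is not shown.

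All of this limits the concern. It does not remove the order in 14.4, which the protocol itself fixes, nor the printed meaning of the only letters it provides.

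**Conclusion.** The point holds in a limited form. That the first unblinding precedes database lock follows directly from sections 14.4 and 11.1.3, so queries and ITT/per-protocol classification could be settled after it. That the analyst's blinding is not secured is conditional: it assumes that the first step releases the Appendix 7 letters, or the arms by name, to people who handle or analyse the data. The protocol neither says so nor rules it out.

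The order applies to the data of all 66 planned participants, but the documents do not show that anyone would in fact learn the arms. The size of any bias cannot be computed. The case for changing the text is that the order serves no evident purpose, since entry and verification do not require group codes, and that correcting it costs almost nothing.

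**What to change.** Rewrite the closing part of section 14.4 so that the first unblinding follows, in this order, double entry, query resolution, classification of the ITT and per-protocol sets, and a documented database lock. State that it releases group codes only, and only to the analyst. Refer to the lock in section 11.1.3 so that the two sections give one sequence.

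Use neutral analysis codes that differ from the letters on Appendix 7. Keep the code key and the completed Appendix 7 forms with someone outside data entry and analysis, for example the researcher who prepared the envelopes, and release the key only at the second unblinding. Appendix 7 can then keep its arm names. Deleting them would remove the only explicit link between letter and arm in the document, without saying where that link is to be held.

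The cost is minor administrative work: a revised passage in 14.4, a set of neutral codes and a named custodian. Treatment, visits and sample size are unaffected.
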